## Abstract

**Background:**

This randomized controlled trial aims to evaluate the effects of an early developmental intervention program on the development of young children in low- and low-middle-income countries who are at risk for neurodevelopmental disability because of birth asphyxia. A group of children without perinatal complications are evaluated in the same protocol to compare the effects of early developmental intervention in healthy infants in the same communities. Birth asphyxia is the leading specific cause of neonatal mortality in low- and low-middle-income countries and is also the main cause of neonatal and long-term morbidity including mental retardation, cerebral palsy, and other neurodevelopmental disorders. Mortality and morbidity from birth asphyxia disproportionately affect more infants in low- and low-middle-income countries, particularly those from the lowest socioeconomic groups. There is evidence that relatively inexpensive programs of early developmental intervention, delivered during home visit by parent trainers, are capable of improving neurodevelopment in infants following brain insult due to birth asphyxia.

**Methods/Design:**

This trial is a block-randomized controlled trial that has enrolled 174 children with birth asphyxia and 257 without perinatal complications, comparing early developmental intervention plus health and safety counseling to the control intervention receiving health and safety counseling only, in sites in India, Pakistan, and Zambia. The interventions are delivered in home visits every two weeks by parent trainers from 2 weeks after birth until age 36 months. The primary outcome of the trial is cognitive development, and secondary outcomes include social-emotional and motor development. Child, parent, and family characteristics and number of home visits completed are evaluated as moderating factors.

**Discussion:**

The trial is supervised by a trial steering committee, and an independent data monitoring committee monitors the trial. Findings from this trial have the potential to inform about strategies for reducing neurodevelopmental disabilities in at-risk young children in low and middle income countries.

**Trial Registration:**

Clinicaltrials.gov NCT00639184

## Background

### Research justification

Birth asphyxia, or failure to initiate spontaneous respiration, is the leading specific cause of neonatal mortality in low- and low-middle income countries (L/LMIC) and accounts for about one million the four million neonatal deaths that occur each year worldwide [1]. Birth asphyxia is also the main cause of neonatal encephalopathy [1-3] and long-term morbidity including intellectual disability, cerebral palsy, and other neurodevelopmental disorders [2-4]. Mortality and morbidity from birth asphyxia disproportionately affect more infants in L/LMIC, particularly those from the lowest socioeconomic groups [5]. Therefore, neonatal resuscitation is being implemented through formal training programs in many L/LMIC [6,7]. Although improving resuscitation in L/LMIC may save lives, this intervention may also increase the number of survivors at risk for neurodevelopmental impairment. This has not been evaluated well in L/LMIC. However, prior empirical findings suggest that low cost, home-based, parent-provided early developmental interventions can reduce this risk and improve developmental outcomes in children [8].

### Sequelae of birth asphyxia

Birth asphyxia can result in hypoxic-ischemic brain injury that selectively affects vulnerable areas of the immature brain. The type of neurodevelopmental sequelae, as determined by the specific area of the brain damaged and by the severity, duration, and timing of the insult, can include cognitive disabilities such as mental retardation, motor disabilities, and visual and hearing impairment [e.g, [4,9]]. Even in the absence of mental retardation, children surviving birth asphyxia may display general cognitive abilities in the lower range of normal and learning disabilities. Sociocultural factors found in L/LMIC, such as poverty, illiteracy, low status of women, poor hygiene, lack of clean water and sanitation, and inadequate access to health care and social services exacerbate the risk for neurodevelopmental disability following birth asphyxia [10].

### Early developmental intervention

Programs of early developmental intervention (EDI) are capable of preventing or limiting the declines in cognitive development that may occur in the first years of life following brain insult. EDI has been defined as a broad array of activities designed to enhance a young child's development [11]. EDI interventions are intended to affect children directly via structured experiences and indirectly through influencing the care giving environment. These services can be provided in a variety of contexts, including home, center, hospital, and/or clinic, with the intensity of the interventions being based on the child's and family's needs and resources, the cultural milieu, and access to trained professionals. The primary goals for EDI include improving the child's developmental trajectories and assisting the family in addressing the needs of a child with, or at risk for, developmental delays.

The positive effects of EDI on early child development have been demonstrated in numerous controlled trials in the US and other high-income countries [e.g., [12-17]], which have been confirmed through meta-analyses [18,19] as well as expert reviews [e.g., [16,20,21]]. The average effect size across studies evaluating EDI has ranged from 0.50 - 0.75 [21,22].

### Early developmental intervention in L/LMIC

The effects of EDI on early child development in infants with birth asphyxia in L/LMIC have not been evaluated sufficiently to determine if these interventions should become standard practice. We are aware of only one small single-center randomized controlled trial targeting the risk group of infants with birth asphyxia. Conducted in China [23], the effects of EDI were evaluated in 64 infants with birth asphyxia, who were randomized to EDI (n = 34) or conventional care (n = 30). A group of term infants (n = 38) without birth asphyxia was also provided conventional care for comparison. A relatively low-intensity home-based, parent-provided intervention included home visits to teach the parents how to provide stimulating activities with their infants. Following two visits in the first month, subsequent home-visit were made monthly during the first year and then every two months in the second year, when parents received continued instruction to apply age-appropriate stimulation activities with their infants.

Neurodevelopmental assessment performed by a masked trained evaluator using a modified Bayley Scales of Infant Development (BSID) [24] at 18-24 months, documented mental development index (MDI) for asphyxiated infants of 105 ± 15 in the EDI group vs. 91 ± 11 in the conventional care group (*p *< 0.001). Normal term infants who received conventional care and obtained a MDI of 100 ± 13. The BSID psychomotor development index (PDI) did not differ significantly between the groups. This trial suggests that a program of EDI, at a level of intensity lower than evaluated in high-income countries, may effectively promote cognitive development in infants with birth asphyxia. The effect size was about 1.0 standard deviation (SD). Nonetheless, it is unknown if the cognitive benefits are reproducible and generalizable because of the limited scope of the trial and the small sample size.

Several trials of EDI with other risk groups of infants and young children conducted in different L/LMIC, uniformly document its positive effects on child development. This has included groups at risk for neurodevelopmental disability due to *prematurity or low birth weight *in China [25] and Jamaica [26,27]; *growth retardation or stunting *in Jamaica [28-30]; *malnourishment *in Colombia [31,32], Jamaica [33-36], India [37], and Bangladesh [38,39]; as well as *socioeconomic deprivation *in Jamaica [40], Brazil [41] and Vietnam [42]. Follow-up evaluations as long as 18 years have shown significant positive effects for those who received EDI during the first two years of life on measures of intelligence, reading comprehension, mental health, and self-esteem [43,44].

While several studies have suggested positive effects on the development of children at risk for neurodevelopmental disabilities in a number of L/LMIC, most enrolled relatively small samples. Thus, a larger, multi-site study is needed to evaluate EDI in L/LMIC.

### Background information on the trial

The Brain Research to Ameliorate Impaired Neurodevelopment - Home-based Intervention Trial (BRAIN-HIT) was conducted in communities in India, Pakistan, and Zambia that participated the Global Network for Women's and Children's Health Research and are sites of the FIRST BREATH (FB) Trial. The FB Trial was the first randomized trial to test the effectiveness of standard educational programs for resuscitation interventions (initial steps of resuscitation and bag and mask ventilation) to reduce mortality from birth asphyxia (ClinicalTrials.gov). The FB Trial was developed to answer the question of whether increased resuscitation efforts would be associated with an increase of survivors at-risk for neurodevelopmental disability in societies least able to provide for their care. Therefore, BRAIN-HIT is a follow-up trial of a sub-set of the FB Trial infants who were resuscitated by bag and mask ventilation. BRAIN-HIT is designed to evaluate whether EDI can improve neurodevelopment in infants at-risk for poor neurodevelopment outcome due to birth asphyxia.

### Trial sites

BRAIN-HIT is implemented at sites in India (Jawaharlal Nehru Medical College, Belgaum), Pakistan (The Aga Khan University, Karachi), and Zambia (University Teaching Hospital/University of Zambia School of Medicine, Lusaka). In addition, RTI International serves as the data coordinating center for the trial. Sites in India, Pakistan, and Zambia were selected for the BRAIN-HIT because these countries have well organized primary care health systems yet a high proportion of home deliveries attended by traditional birth attendants and a majority of home deliveries. Birth asphyxia is a major cause of neonatal mortality and neurodevelopmental disability in all three countries. The study sites in India, Pakistan and Zambia are relatively rural and have a high perinatal mortality rate. The India site was located in Karnataka State; in Pakistan, the site was in Thatta, about 100 kilometers from Karachi; and in Zambia, the site was located in Chongwe and Kafue Districts, about 100 kilometers from Lusaka.

### Formative and feasibility research

Prior to embarking on BRAIN-HIT, investigators tested the feasibility of the methods over a two-year period in Zambia. Funded with a planning grant from the NIH Fogarty International Center, pilot work included perinatal data collection, identification of infants with birth asphyxia (Ellis neurological exam and Apgar scoring), recruitment of at risk infants, administration of the EDI program, and neurodevelopmental testing. Indicated modifications in the methods were made before implementation of the current RCT.

### Aim, objectives, and hypotheses

The *overall aim *of BRAIN-HIT is to evaluate the effects of an EDI program on the development of children in L/LMIC who are at-risk for neurodevelopmental disability because of birth asphyxia. A group of children without perinatal complications are evaluated in the same protocol to compare the effects of the EDI in healthy infants in the same communities. If the study shows positive results, the long-term aim is to empower local health systems with training and logistic support to sustain an EDI program that can reduce morbidity for children in L/LMIC with high rates of birth asphyxia as well as stimulate further research and implementation of comparable programs worldwide.

The *specific objectives *are to: (1) Evaluate the effects of a home-based EDI plus health and safety counseling (HSC) compared to HSC alone on the cognitive, social-emotional, and motor development at 12, 24 and 36 months in children with birth asphyxia; (2) Determine whether children with birth asphyxia who receive EDI demonstrate cognitive, social-emotional and motor development at 12, 24 and 36 months of age that is indistinguishable from that of children without perinatal complications from the same communities; and (3) Examine whether the effects of EDI on children with birth asphyxia are moderated by child, parent, and family characteristics.

The *primary hypothesis *is that home-based EDI and HSC will improve cognitive development (as indicated by a difference in BSID MDI scores of 10 points [0.67 SD]) at 36 months of age compared to HSC only, in children with mild to moderate birth asphyxia and normal post-natal neurological exam. This hypothesis is also tested in groups of children without perinatal complications from the same communities. The following *secondary hypotheses *are also tested in children with and without birth asphyxia: (1) Improvements will be observed in children who receive EDI in social-emotional and motor development at 36 months of age compared to those who do not; (2) Improvements will be observed in children who receive EDI in all developmental domains at 12 and 24 months of age; compared to those who do not (3) The improvements in cognitive, social-emotional, and motor development related to EDI will be larger in the children with birth asphyxia compared to those without perinatal complications; (4) The effects of EDI in children with and without birth asphyxia will be moderated by child, parent, and family characteristics; and (5) Children who receive a higher EDI dose (i.e., are exposed to more EDI home visits by a parent trainer) will experience greater developmental improvements than those who receive a lower dose.

## Methods/Design

### Design

The study sample for this RCT was drawn from two populations. The birth asphyxia group had mild-to-moderate birth asphyxia, was resuscitated at birth, and had a neurological examination consistent with normal or Stage I-II on the Ellis scale in the first week of life. The group without birth asphyxia constituted a comparison group of children who were not resuscitated and had experienced no perinatal complications. Within each group, children and their mothers were randomized to either the intervention arm (EDI + HSC) or the control arm (HSC only).

To ensure that any effect of the intervention was related to the curriculum used in the home visits of the EDI, rather than simply to having a number of visits from a provider, parents in the control condition receive visits on the same schedule (every two weeks) throughout the three years of the trial as those in the intervention arm. However, only HSC is provided to participants in the control condition. This intervention trial cannot be fully masked, as the parents and the parent trainers are aware of which condition they are in, but to reduce bias, the evaluators administering the 12, 24 and 36 month assessments are blinded to the treatment assignments.

### Randomization

The data center generated randomization lists for infants with and without birth asphyxia, using a block randomization procedure (randomization occurred within blocks of 4 or 8). Each site was provided with sealed envelopes with the randomization assignment. For each randomized infant with birth asphyxia, the sites then randomized the next one to two infants without birth asphyxia so that an overall ratio of approximately 1-to-2 was achieved.

### Interventions

#### Experimental: Early Developmental Intervention

A home-based, parent-implemented EDI model was chosen because the home is the foremost natural environment for learning to occur for a child aged birth to three, and the parent (or the equivalent) is one of the limited numbers of caring persons with whom the infant or toddler is attached [11,21]. This approach supports the parent in the role as the first teacher of the child and provides opportunities for strengthening the parent-child bond. This model is also especially well suited for low-resource settings because it requires relatively little infrastructure and resources to implement compared to alternative model, such as center-based interventions. The EDI will be provided over the first 36 months of children's lives. While the intervention in the vast majority of cases will target the mother, fathers as well as extended family members are welcomed additional participants.

#### Curriculum

The *Partners for Learning *[45] curriculum and supplemental materials provide the structure and substance of the EDI. This curriculum served as the core intervention in two of the first large-scale RCT evaluations of EDI in the U.S. [17,46], which demonstrated significant cognitive, language, and social gains and long-lasting improvement in educational achievement and social outcomes for children at risk for developmental problems who participated in this program. In addition, research has shown that the *Partners for Learning *curriculum can be implemented effectively in home visitation programs for children at high risk due to low birth weight [13,47].

*Partners for Learning *has several components that are transmitted via a trainer who visits parents in the children's homes. During each visit, the trainer presents playful interactive learning activities, which are depicted on cards. Each activity targets a developmentally appropriate competence Cycles of use allow the parent to implement several activities for a while, but then move on to new activities as the child masters each competence. This progression is guided by the trainer, who selects activities to match and enhance the child's developmental competences. *Partners for Learning *covers a full spectrum of 23 developmental skill areas, organized into the four areas: (1) cognitive and fine motor, (2) social and self-help, (3) gross motor, and (4) language skills. The trainer encourages the parent to apply the targeted activities until the next home visit by integrating them into daily life with the child. The activities can thus enrich care routines such as diapering, feeding, dressing and special one-to-one times. By applying these activities and observing how the child changes and acquires these competences, general principles gradually emerge that enable the parent to gain a deeper understanding of early child development. With this understanding, the parent can appreciate her own important contribution to the child's development, thereby gain enhanced efficacy in the parenting role and become empowered as an important agent in the child's life.

#### Staff, training, and implementation

Each site selected EDI trainers and supervisors with appropriate backgrounds to its context, such as education, nursing, public health, and physiotherapy. The trainers conducting the EDI home visits and the supervisors initially participated in a five-day workshop conducted at each research site by experienced EDI professionals from the U.S.. The training covered expectations, rationale, early child development, home visiting procedures, the *Partners for Learning *curriculum and materials, assessment and monitoring of progress, and partnering with parents. Also the Portage Model of home visiting [48] was stressed as a way for the EDI trainers to structure their approach to working with mothers (and other family members) during each visit. The training included practice and feedback. A second workshop was conducted at each site when participating children began to reach age 18 months. While some of the same material was reviewed as at the first workshop, this workshop focused on adapting EDI procedures for the children as they develop and observing trainers in actual home visits, to provide constructive feedback.

Each parent-child pair has an assigned trainer conducting the home visits, which are scheduled to occur every two weeks. A form is used to record each visit and which activities were addressed. One to two activities are taught to the parent at each visit. The trainer demonstrates the activity with the child and explains its value. The parent then practices the activity with the child and is given encouraging feedback to fine-tune her interaction with the child. The parent is given the card demonstrating each activity that has been addressed in the visit and is instructed to apply the activities as frequently as possible in her everyday interactions with the child until the next visit.

#### Control: Health and Safety Counseling

A modified version of the World Health Organization health education curriculum http://www.who.int constituted the Health and Safety Counseling (HSC) curriculum used in both arms of the trial. A range of health and safety issues are addressed over time, for example breastfeeding, nutrition, hygiene, safety in the home and community, management of child diarrhea, and well-child check-ups and vaccinations. This material is discussed with the parent during home visits on the same schedule as the EDI. While participants in the experimental condition also receive HSC in addition to EDI, those in the control condition receive only HSC.

### Duration

Both the experimental and control conditions are implemented over the child's first 36 months of life, in the form of home visits every two weeks. Each intervention visit is designed to take 30 to 45 minutes. The developmental and health assessments to address the hypotheses are conducted at child ages 12, 24, and 36 months. These assessments generally take two to three hours.

### Enrollment

The primary population is children born in the delivery services of the health care centers/hospitals in Lusaka, Zambia or in rural communities in India, Pakistan, and Zambia participating in the FB Trial. Specific eligibility criteria included: a child with (1) birth asphyxia defined as requiring bag-and-mask resuscitation; (2) birth weight ≥ 1,500 g; (3) neurological examination consistent with mild or moderate (Stage I or II) status on the Ellis scale (Ellis et al. 2000); and (4) a parent who is willing to participate in an intervention program for 36 months. The few children who survive severe birth asphyxia and have severely impaired neurological examinations (Ellis Stage III) are excluded because they have a very high infant mortality rate and are unlikely to benefit from EDI [49]. A healthy comparison group of children without birth asphyxia or other perinatal complications (Apgar > 6 at 5 minutes) and with a birth weight ≥ 1500 g and Ellis Stage I or II rating during the first week are recruited from the same delivery centers and communities over the same time span. All enrolled participants complete approved informed consent procedures. Parents are compensated for travel and the time taken and wages lost to complete the 12, 24, and 36 month evaluations.

### Power analysis

The primary hypothesis is that a home-based EDI plus HSC compared to HSC alone will improve the BSID MDI at 36 months by 10 points in children with birth asphyxia. At least 40 participants per condition who complete the 36 month assessment in each randomization group (birth asphyxia and healthy comparison group) will be needed to be able to detect the hypothesized difference of 10 MDI points (= 0.67 SD) between the experimental and control condition with 5% level of significance and 90% power [50,51]. Assuming 10% attrition per year and possible missing values, at least 60 children per condition and group, or at least 120 children with birth asphyxia and 120 healthy comparison children for a total of 240, need to be enrolled and randomized to either EDI plus HSC or HSC alone to achieve the desired power.

Consequently, at least 80 children (40 in each group) were to be enrolled in each country. However, due to anticipated higher attrition in the healthy comparison group, the sites were to enroll additional children from this group. In total, 431 children across the two groups have been enrolled and randomized during the defined enrollment period, including 174 in the birth asphyxia and 257 in the healthy comparison group.

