### Data analysis

The primary outcome for the study will be analyzed using an intent-to-treat strategy, where data for all participants who meet the inclusion/exclusion criteria will be included in the analysis, regardless of how many home visits are completed. Secondary analyses will be conducted to evaluate the impact of the adherence to the study protocol (e.g., number of visits) on the relationship of the intervention to study outcomes. Because of high post-neonatal childhood mortality (5%), particularly in the group with asphyxia, some attrition is expected.

Comparisons of MDI between the two trial conditions at the end of the study will employ student's t-test, which are repeated for the birth asphyxia and health comparison groups. Descriptive statistics will be reported as frequencies and percentages for categorical variables and means, standard deviations, and minimum and maximum values for continuous variables. Additionally, generalizing estimating equations models and hierarchical linear modeling will be used to perform the analysis on the primary and secondary outcome variables. Other secondary data analyses involving continuous outcomes will be performed using multivariate analysis. Simple ordinary regression models for continuous models will be used to analyze within treatment group differences in outcomes.

To determine cost-effectiveness, the incremental cost of sustaining a home-based early intervention program will be compared to the "willingness to pay" for a disability-adjusted life year (DALY). Maintenance of a home-based intervention program has a relatively low incremental cost from a programmatic standpoint. The incremental cost per year once the program is established will be the salary of a full time trainer, training equipment, transportation, and supplies. For example, experimental research in Lusaka, Zambia has shown that if the rate of MDI <70 due to birth asphyxia is reduced from 7 to 3.5%, the incremental cost will be around $8.50 per DALY ($22,000 ÷ [3.5/100 absolute risk reduction × 2000 survivors of asphyxia enrolled per year × 37 years life expectancy]). This cost compares favorably with that of other medical procedures [60].

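### The 90% power stated for 40 completers per arm holds only for a one-sided 5% test that the protocol never declares; two-sided it is about 84%

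*Protocol article*

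**What the plan says.** The Power analysis section of the protocol article sets the target difference as the "hypothesized difference of 10 MDI points (= 0.67 SD"), which implies an SD of about 15. The same pair of figures appears under Aim, objectives, and hypotheses. The completer requirement is "At least 40 participants per condition who complete the 36 month assessment in each randomization group", and the difference is to be detected "between the experimental and control condition with 5% level of significance and 90% power".

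Allowing for 10% attrition per year and some missing values, the section concludes that "at least 60 children per condition and group, or at least 120 children with birth asphyxia and 120 healthy comparison children" must be enrolled. It then reports that 174 children with birth asphyxia and 257 comparison children were in fact enrolled.

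The Data analysis section names the test: "Comparisons of MDI between the two trial conditions at the end of the study will employ student's t-test", repeated in each group. Neither section says whether the test is one-sided or two-sided, and nothing else in the article does. The hypothesis is worded directionally: the intervention "will improve the BSID MDI at 36 months by 10 points in children with birth asphyxia".

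**The concern.** Apart from sidedness, the inputs to the sample size are stated or directly implied, so it can be checked. A 5% significance level given without qualification, with a Student's t-test, is ordinarily read as two-sided. On that reading 40 per arm does not give 90% power.

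Two things are at stake. The first is whether the stated power, the floor of 40 completers and the enrolment minimum of 60 per condition mean what they say. The second is the critical value of the primary test. A one-sided test at the full 5% allows twice the false-positive rate in the direction of benefit that a two-sided 5% test allows (5% against 2.5%). A result falling between the two thresholds could be read either way unless the choice is fixed in writing before the 36-month data are analysed.

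**Working it through.** **Inputs**

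- Difference 10 points, stated as 0.67 SD (Power analysis). The SD is not given separately; 10/0.67 ≈ 15. Both d = 10/15 = 0.667 and d = 0.67 are used.
- α = 0.05, sides not stated; power 0.90; 40 completers per condition; equal arms (Power analysis).
- Test: two-sample Student's t-test in each group (Data analysis).
- Attrition 10% per year for three years, so retention is 0.9³ = 0.729.

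**Step 1. Reproduce the plan's figure.** By normal approximation, n per arm = 2(z_α + z_β)²/d², with z_β = 1.2816 for 90% power.

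- One-sided 5%: z_α = 1.6449, so n = 2(1.6449 + 1.2816)²/0.667² = 38.5, rounded up to 39. The exact (noncentral t) calculation gives 39.2, rounded up to 40.
- Two-sided 5%: z_α = 1.9600, so n = 2(1.9600 + 1.2816)²/0.667² = 47.3, rounded up to 48. The noncentral t gives 48.3, rounded up to 49. With d = 0.67 it gives 47.8, rounded up to 48.

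The stated 40 per arm is therefore the one-sided answer.

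**Step 2. Power at 40 completers per arm.** The noncentrality parameter is d√(n/2) = 0.667 × √20 = 2.98, on 78 degrees of freedom.

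| Test at 5% | d = 10/15 | d = 0.67 |
|---|---|---|
| One-sided | 90.5% | 90.7% |
| Two-sided | 83.8% | 84.1% |

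Two-sided, the difference detectable with 90% power at 40 per arm is 11.0 points rather than 10.

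**Step 3. The enrolment minimum.** 60 × 0.729 = 43.7 completers per condition.

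- Two-sided: power about 87% (86.9% for d = 10/15), before any missing values among those retained.
- One-sided: power about 93%. Only 40/0.729 = 54.9, so 55 enrolled per condition, would be needed, and 60 leaves a margin for missing values.
- Two-sided enrolment for 90%: 48/0.729 = 65.8, so 66 per condition (132 per group), or 49/0.729 = 67.2, so 68 per condition (136 per group), against the stated 120 per group.

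**Step 4. What the actual enrolment delivers, two-sided.** The split between arms is not reported; equal arms are assumed.

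- Birth asphyxia: 174/2 = 87; 87 × 0.729 = 63.4 completers per arm; power about 96%.
- Comparison group: 257/2 = 128.5; 128.5 × 0.729 = 93.7 completers per arm; power about 99.5%.

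**The case against.** The strongest reply is that the figure reproduces exactly from the article's own inputs once the test is taken as one-sided, and the hypothesis is directional throughout. The article attributes the calculation to cited references that are not at hand, and it condenses a fuller protocol. On the one-sided reading the 60 per condition is also adequate. Silence on sidedness does not establish a two-sided test.

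Much of this stands. A reader might infer that the 90% is simply an arithmetic error, and the document does not support that: one undeclared but possible choice gives exactly 40. A reader might also infer that the trial is underpowered, and the document does not support that either. Enrolment had already passed the two-sided requirement. For the birth asphyxia group to fall to 40 per arm, 47 of about 87 children per arm (54%) would have to be lost, against the 27% implied by the stated attrition.

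What does not stand is that directional wording settles the matter. Superiority hypotheses are commonly worded as improvements and tested two-sided, and a one-sided test at the full 5% is unusual enough to need declaring. Nor is this detail that can be left to a fuller document: the article chose to state a power figure, and sidedness decides whether that figure is true.

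**Conclusion.** The power statement holds only for a one-sided 5% t-test that the article does not declare. On the conventional two-sided reading, 40 completers per arm give about 84% power, 90% needs 48 to 49 per arm, and the planned 60 per condition yields about 44 completers and about 87%.

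This rests on an SD of about 15 (implied by 10 points = 0.67 SD), equal arms, and attrition compounding at 10% per year. The range of 48 to 49 reflects only whether d is taken as 0.67 or 10/15.

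Severity is minor to moderate. The planning figure and the completer floor need clarifying, but the sample already enrolled exceeds 90% power on either reading at the stated attrition.

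**What to change.** State in the Data analysis section whether the primary t-test is one-sided or two-sided, and make the Power analysis section match.

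- If two-sided: restate the power as about 84% at 40 completers per arm, give 48 to 49 per arm as the floor for 90%, and report the power delivered by the enrolled 174 and 257 at the assumed attrition (about 96% and above 99%, assuming equal arms) in place of the basis of 120 per group.
- If one-sided 5% was intended: declare it explicitly, in both sections. The 40 and the 60 then stand.

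The choice is the investigators' to make and should be recorded before the 36-month outcomes are analysed. The cost is wording only: no extra enrolment and no change to the conduct of the trial.
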